### Randomization and blinding procedures

2.5

There will be 4 assignments according to the order of the bloodletting devices (T = test device, C = control device) and blood collection location (L = left, R = right): RTLC (group A), LTRC (group B), RCLT (group C), and LCRT (group D). Balanced block randomization will be used to evenly assign the participants to each group. The process will be as follows:

1.number the assignment for each group (A = group A, B = group B, C = group C, D = group D),2.randomly select 1 block size among 4, 8, 12, and 16,3.randomly select 1 sequence that can be allocated to 4 groups evenly for each block size,4.assign participants to the selected sequence, and5.repeat steps 2 to 4 for 100 participants.

Participants who meet all registration criteria will be randomly assigned to a randomization identification code (e.g., BCU-R-001, BCU-R-002, …, BCU-R-036) in the order generated by a computer randomized program. The randomization identification code indicates the type of bloodletting device and the order of the left and right hands. Additionally, the participants and the assessors who will be collecting the data will be blinded to the group allocation.

Information of the intervention assignment will be stored in the 3rd statistical department. The randomization code will be placed in an opaque envelope and stored in the hospital. With the exception of disclosure to individual patients in emergency situations, randomization, and blinding will not be disclosed to researchers until the end of the trial.

### Intervention

2.6

The test device (ROAH-L-NO1) will be manufactured by Roahmed Medical Device Co. (Changwon, Republic of Korea), and the control device (LANZO 1.5) will be manufactured by GMMC Medical Device Co (Seoul, Republic of Korea). Both devices will be applied to the participants’ 3rd finger.

All eligible participants will receive a treatment according to the allocated group, RTLC, LTRC, RCLT, or LCRT, on the day of the screening visit. To maintain the double-blinded nature of the study, during the procedure, a screen will be placed between the participant and the operator. The operator will use the test and control devices on the participants on the outside of the screen, and participants will be indistinguishable to which hand the test device is assigned. The operator will practice using the randomized device on the 3rd finger of 1 hand of the participant. If blood is collected to the extent that the blood glucose level can be measured, it will be determined to be successful, and the 1st measurement will be completed. If no blood is collected, the participant will be checked to confirm no bleeding (“nonbleeding”), and treatment will be applied again after 10 minutes to determine whether blood collection is successful. When the total number of instances of nonbleeding is 3, no further procedure will be recorded, and “blood collection failure” will be recorded. The operator will check the participants’ state of hemostasis after bleeding, and if hemostasis does not occur within 3 minutes (“delayed hemostasis”), the participant will be checked again for complete hemostasis. If hemostasis does not occur for more than 10 minutes, the operator will check the participant for hemostasis abnormalities, and the operator will stop the clinical trial and seek medical attention for the participant. The secondary measurement will be performed 10 minutes after the primary measurement in the same way on the same area of the participants’ opposite hand. Participants will undergo the intervention from 1 to 3 times only on the day of the procedure.

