## Abstract

**Background::**

The bloodletting device has been used by many institutions for about 100 years. Many patients feel fear from the pain caused by applying the bloodletting device for treatment. We used bloodletting device using the principle of “prestimulation neurodisturbance,” which can mask the subject undetectable for pain. In this study, we will investigate pain of bloodletting device during blood collection and will identify the safety of the device.

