### Outcome measures

2.7

The primary outcome will be the VAS score, which will be assessed upon successful blood collection. The secondary outcomes will be the verbal rating scale (VRS) score and the time at which pain disappears after blood collection (second), which will be assessed upon successful blood collection. In addition, the total number of nonbleeding cases, number of blood collection failures, number of cases of delayed hemostasis, and number of participants will be counted. Participants’ data will be anonymized and coded by a specific program.

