### Statistical analysis

2.9

Statistical analysis will be primarily based on the principle of the full analysis set. Missing values will be analyzed by the last observation carried forward method. For each of the 2 devices, the VAS score and time at which the participant's pain disappears will be measured, and descriptive statistics will be presented as a mean, standard deviation, median, and minimum and maximum values. The analysis method for evaluation of the variables of efficacy will involve confirmation of the normality of the values and then comparison using the paired *t* test or Wilcoxon signed-rank test. The McNemar test will be used to analyze the VRS score, total number of nonbleeding cases, number of blood collection failures, number of cases of delayed hemostasis, and number of participants. The significance level will be set at *P* < .05 and the confidence interval at 95%. All statistical analyses will be performed using SPSS Statistics for Windows version 20.0 (IBM Corp, Armonk, NY).

If necessary, subgroup analyses of outcome variables, such as the demographic variables measured at baseline (e.g., sex, age, duration of illness, treatment expectation) can be performed. Safety assessments will be performed primarily by analyzing the frequency of adverse events and serious adverse events (SAEs) that researchers suspect to be related to treatment. The collected safety data will be summarized appropriately. All adverse events that occur will be listed with a detailed description. All SAEs will be recorded descriptively. The adverse events will be collected through patient symptom reporting and researcher observation. The frequency of each adverse event associated with or unrelated to the intervention will be recorded and analyzed using descriptive statistics. There is no intermediate analysis of this study, and the final decision regarding the completion of the clinical trial will be made by the PI.

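### After a first-hand bleed of more than 10 minutes, LOCF would copy the event to a device that was never used, and the McNemar comparison of delayed hemostasis loses it

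*Protocol article*

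**What the plan says.** All references are to the protocol article.

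- **Outcome.** Section 2.6 defines the event at 3 minutes: "if hemostasis does not occur within 3 minutes (“delayed hemostasis”), the participant will be checked again for complete hemostasis".
- **Stop.** Once bleeding has gone on past 10 minutes, the same section says that "the operator will check the participant for hemostasis abnormalities, and the operator will stop the clinical trial and seek medical attention for the participant". I read this as a stop for that participant, not for the whole trial.
- **Second device.** Also in 2.6: "The secondary measurement will be performed 10 minutes after the primary measurement in the same way on the same area", on the other hand.
- **Counting.** Section 2.7 lists among the outcomes: "number of cases of delayed hemostasis, and number of participants will be counted". It does not require a completed pair.
- **Test.** Section 2.9 says: "The McNemar test will be used to analyze the VRS score, total number of nonbleeding cases, number of blood collection failures, number of cases of"; the list then goes on to delayed hemostasis. The same section bases the analysis on the full analysis set and prescribes LOCF for missing values, with no exception by outcome or device.
- **Aim.** The abstract says that the study "will identify the safety of the device".

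**The concern.** McNemar needs a result from each hand and draws only on discordant pairs. A first-hand bleed of more than 10 minutes already meets the 3-minute definition, but it also triggers the stop, so the other hand normally has no result. The missing value is caused by the outcome being compared.

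The rule the plan states for missing values makes this worse. In this design the last observation before the missing one belongs to the other device. Carrying it forward records a delayed-hemostasis event for a device that never touched the participant. The pair becomes yes/yes and contributes nothing to the test. If LOCF is not applied, the pair is incomplete and contributes nothing either. The same bleed on the second hand comes with a complete pair and can count.

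At stake is the one stated between-device test of hemostasis, in a study that names safety as an aim.

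**Working it through.** The article states no hemostasis rate, margin or power, so there is no figure of the plan to reproduce. What follows is an illustration on assumed rates.

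**From the article.** N = 100 (2.1). Two of the four balanced groups start with the test device and two with the control (2.5), so about 50 participants per order. The event is bleeding over 3 minutes and the stop comes at over 10 minutes (2.6).

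**Assumed.** pT and pC are the probabilities of delayed hemostasis (over 3 minutes) on test and control. qT and qC are the shares of those events that last over 10 minutes. The two hands are independent. The second device is not applied after a first-hand event over 10 minutes.

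**Step 1: discordant pairs if both hands were always done.** Test only: b = 100·pT·(1 − pC). Control only: c = 100·pC·(1 − pT).

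**Step 2: discordant pairs under the stop.** A first-hand event over 10 minutes leaves no discordant pair, whether the pair is dropped or made concordant by LOCF:

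- b = 50·pT·(1 − qT)·(1 − pC) + 50·pT·(1 − pC), which is the step 1 value times (1 − qT/2)
- c = 50·pC·(1 − pT) + 50·pC·(1 − qC)·(1 − pT), which is the step 1 value times (1 − qC/2)

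Incomplete pairs: 50·(pT·qT + pC·qC). The ratio b/c is multiplied by (2 − qT)/(2 − qC), which is 1 when the shares are equal.

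**Step 3: numbers.**

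| pT | pC | qT | qC | b, c all pairs | b, c under the stop | b/c before, after |
|---|---|---|---|---|---|---|
| 10% | 5% | 10% | 10% | 9.50, 4.50 | 9.025, 4.275 | 2.11, 2.11 |
| 10% | 5% | 50% | 50% | 9.50, 4.50 | 7.125, 3.375 | 2.11, 2.11 |
| 5% | 5% | 50% | 50% | 4.75, 4.75 | 3.56, 3.56 | 1.00, 1.00 |
| 10% | 10% | 50% | 10% | 9.00, 9.00 | 6.75, 8.55 | 1.00, 0.79 |
| 10% | 10% | 10% | 50% | 9.00, 9.00 | 8.55, 6.75 | 1.00, 1.27 |

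Row 1: incomplete pairs 50 × (0.010 + 0.005) = 0.75. Row 2: 50 × (0.050 + 0.025) = 3.75. In row 2 the difference on complete pairs is (7.125 − 3.375)/96.25 = 3.9%, against 5.0% with all pairs. In rows 4 and 5 the delayed-hemostasis rates are equal, and the device with more events over 10 minutes looks better.

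**Step 4: what LOCF does to the counts (row 2).**

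- Control: 50 × 0.05 = 2.5 first-hand events, plus 50 × (0.05 copied + 0.95 × 0.05) = 4.875 in the second position. Total 7.375, against 5 if every control hand were done.
- Test: 5 + 50 × (0.025 copied + 0.975 × 0.10) = 11.125, against 10.
- Both counts rise through copied events, and the difference falls from 5 to 3.75.

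**Step 5: what the raw count keeps without LOCF (row 2).** Test cases: 5 + 50 × 0.975 × 0.10 = 9.875, against 10. Only second hands that were not done are lost; first-hand events stay.

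**The case against.** A reader might infer that the worst bleeds vanish and that the safety result is therefore understated. The document does not support that. The event has already met the 3-minute definition when the stop applies, section 2.7 counts cases without requiring a pair, and section 2.9 uses the full analysis set. Section 2.3 does not name prolonged bleeding as a reason for exclusion, although its general clause on inappropriate continuation could be read to cover it. Safety is assessed mainly through adverse events: 2.9 lists them all and 2.10 tests the proportion of participants with at least one, neither of which needs a second hand. Two limits remain. The article does not say that bleeding over 10 minutes is recorded as an adverse event, and a per-participant proportion does not attribute bleeding to a device when most participants receive both.

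A reader might also infer that the comparison shows only half the true rate. With 4% of test hands and no control hands bleeding over 10 minutes, 4 events are expected, 2 fall on the first hand, and 2 of 98 complete pairs (2.0%) show one. But this treats bleeding over 10 minutes as the whole outcome and sets the control rate to zero. Halving is the ceiling of the factor 1 − q/2, reached only at q = 1; the planned outcome starts at 3 minutes.

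Nor does the bias run against one named device. Order is balanced, so the discordant ratio moves only if the shares over 10 minutes differ, and it can move either way.

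Finally, how incomplete pairs enter a secondary test is commonly left to the analysis plan. That is fair, and silence on it is not the point here. The LOCF rule is stated, and followed as written it gives a wrong result.

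**Conclusion.** The point holds as a defect in the hemostasis comparison. Following section 2.9 literally after the stop in 2.6 records an event for an unused device and makes the pair uninformative; not following it leaves the pair out. The comparison loses information, its absolute difference shrinks when the rates differ and the shares are equal, and its discordant ratio is biased in favour of whichever device has the larger share of events over 10 minutes.

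The size cannot be fixed from the document. Under the assumed rates of 10% and 5% it runs from under one pair in 100 (10% share) to just under four (50% share). Because section 2.2 excludes clotting disorders, such events are likely few; that is a judgement, not a documented figure. The conclusion rests on reading the stop as applying to the participant, on the second hand then not being done, and, for the numbers, on independent hands. An understatement of the trial's safety result as a whole is not shown.

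**What to change.** Leave the clinical stop unchanged. In section 2.9:

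- State that LOCF is not applied from one device to the other.
- State that a participant stopped for prolonged bleeding stays in the delayed-hemostasis analysis, with the event counted for the device that was applied.
- Report the proportion with delayed hemostasis per device, with the hands that bled on that device as denominator, alongside McNemar on complete pairs.
- List these stops by device and by first or second hand.

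A comparison of first-hand events by randomised device (about 50 against 50, exact test) can be added as a sensitivity analysis. It does not depend on the second hand, but it is unpaired and less precise than McNemar, so it is optional.

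The cost is a few sentences in 2.9, a cross-reference in 2.6 and one table. No new data are needed.

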### Outcome measures

2.7

The primary outcome will be the VAS score, which will be assessed upon successful blood collection. The secondary outcomes will be the verbal rating scale (VRS) score and the time at which pain disappears after blood collection (second), which will be assessed upon successful blood collection. In addition, the total number of nonbleeding cases, number of blood collection failures, number of cases of delayed hemostasis, and number of participants will be counted. Participants’ data will be anonymized and coded by a specific program.

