### Withdrawal and dropout

2.3

If the participant does not meet the inclusion or exclusion criteria or withdraws his/her consent, or if the participant's continued participation is judged as inappropriate, or if 3 instances of nonbleeding occurs on the same finger of a participant, he/she will be excluded from the study. The researchers will record the reason for any interruption in the intervention and whether each participant completed the study.

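### Pain is scored only at a successful puncture, so nonbleeding punctures go unscored and the device comparison can be biased if nonbleeding differs between devices

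*Protocol article*

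**What the plan says.** Outcome measures (2.7) sets the timing of the primary score: "The primary outcome will be the VAS score, which will be assessed upon successful blood collection". The VRS and the time to pain disappearance are tied to the same moment.

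Intervention (2.6) defines success: "If blood is collected to the extent that the blood glucose level can be measured, it will be determined to be successful". The device is applied "on the 3rd finger of 1 hand of the participant". If there is no blood, "treatment will be applied again after 10 minutes to determine whether blood collection is successful". No pain score is described for the puncture that failed. The sequence ends as follows: "When the total number of instances of nonbleeding is 3, no further procedure will be recorded", and the hand counts as a blood collection failure.

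Withdrawal and dropout (2.3) shows that the repeats fall on one finger, and what follows from three failures: "if 3 instances of nonbleeding occurs on the same finger of a participant, he/she will be excluded from the study".

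Statistical analysis (2.9) says: "Statistical analysis will be primarily based on the principle of the full analysis set". It also says: "Missing values will be analyzed by the last observation carried forward method". VAS is compared between devices by a paired t test or Wilcoxon signed-rank test, with no reference to attempt number. Nonbleeding and collection failures are compared only as separate outcomes, by the McNemar test.

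**The concern.** Whether a puncture bleeds is settled after randomisation and may depend on the device. Making the primary score conditional on it has three consequences:

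- A painful puncture without blood leaves no trace in the pain data.
- The two hands of one participant can be compared at different attempt numbers, one on a fresh finger and one on a finger punctured 10 minutes earlier.
- A device that fails three times on a hand has no score, and the participant is removed for a reason that is itself a device outcome.

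Randomisation and pairing protect a comparison of scores taken at the same point on both hands. They do not protect scores selected by an event that the device may influence. Study design (2.1) sets out to compare the pain of using the devices, and an unsuccessful puncture is also use. The loss is permanent, because no later analysis plan can recover scores that were never taken.

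**Working it through.** **1. What each pattern of punctures yields under the current rules**

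| Pattern on a hand | Score available | Consequence |
|---|---|---|
| Bleeds at puncture 1 | Puncture 1 | As intended |
| Bleeds at puncture 2 or 3 | Puncture 2 or 3, same finger | Earlier punctures unscored |
| Three failures, second hand | None | LOCF would carry over the other device's score: difference forced to 0 |
| Three failures, first hand | None | Nothing to carry forward |

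**2. Conditions for bias**

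Let f be the chance that a puncture does not bleed, independent between punctures. Among hands that succeed within three punctures, the mean number of earlier failed punctures is

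E(f) = [f(1 − f) + 2f²(1 − f)] / (1 − f³).

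If each repeat adds s mm of pain and nothing else operates, the bias (test minus control) is [E(f_T) − E(f_C)] × s.

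- E(0.20) = (0.160 + 0.064)/0.992 = 0.226
- E(0.05) = (0.0475 + 0.00475)/0.999875 = 0.052
- Difference 0.174: about 0.9 mm at s = 5 and about 1.7 mm at s = 10
- Equal rates, or s = 0: no bias by this route

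The second route is a link between a puncture's pain and whether it bleeds. The protocol's own reasoning makes one plausible: the Discussion says that the needle must reach the capillaries and that going too deep is very painful. Shallow punctures may then both hurt less and fail more often.

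**3. Simulation with equal true first-puncture pain**

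The documents give no nonbleeding rates, and no SD in mm could be read from the article's text. All inputs here are assumptions except the limit of three punctures and the 86 pairs (2 × 43, from section 2.4). Assumed: SD 20 mm per score and within-participant correlation 0.5, so the SD of differences is 20 × √(2 × 0.5) = 20 mm. Type I error is for a two-sided 5% test.

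| Nonbleeding, test vs control | Added pain per repeat | Pain–bleeding correlation | Bias in mean VAS | Type I error |
|---|---|---|---|---|
| 10% vs 10% | 5 mm | 0 or 0.4 | 0.0 mm | 5% |
| 20% vs 5% | 0 | 0 | 0.0 mm | 5% |
| 20% vs 5% | 5 mm | 0 | +0.9 mm | 7% |
| 20% vs 5% | 10 mm | 0 | +1.8 mm | 12% |
| 20% vs 5% | 0 | 0.4 | +1.4 mm | 10% |
| 20% vs 5% | 5 mm | 0.4 | +2.2 mm | 18% |
| 30% vs 5% | 10 mm | 0.4 | +5.1 mm | 64% |
| 40% vs 10% | 10 mm | 0.4 | +6.1 mm | 77% |
| 5% vs 20% | 10 mm | 0.4 | −3.1 mm | 30% |

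The first-puncture mean difference was 0.0 mm in every row, within simulation error. The hand formula in step 2 agrees with the two rows in which only the repeat effect operates.

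**4. Hands with no score at all**

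Under independence the share is f³: 0.1% at f = 10%, 0.8% at 20% and 2.7% at 30%. Failures that cluster within people would raise it.

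**5. Scale against the planned effect**

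The plan's 43 per group is reproduced by n = (1.960 + 0.842)²/(2d²) with d = 0.305: 7.849/0.186 = 42.2, rounded up to 43. The effect size as printed, (0.61 ÷ 2) ÷ 3 = 0.102, gives 380 instead. At the assumed SD of 20 mm these two values are 6.1 mm and about 2.0 mm. Until that separate discrepancy is settled, the bias cannot be stated as a share of the planned effect.

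**The case against.** **Pain at the puncture that collects blood is a coherent target.** The Abstract speaks of pain during blood collection. First-puncture scoring has a weakness of its own: if a shallow puncture hurts less and draws no blood, a device that fails to penetrate would look better. The simulation's result that first-puncture scoring is unbiased also follows from taking first-puncture pain as the truth. This objection stands. It is why replacing the primary endpoint is a choice and not a correction.

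**The separate comparison of nonbleeding would show an imbalance.** It would warn of the problem, but it could not supply the missing scores.

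**Stronger readings that the documents do not support:**

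- *The primary comparison is biased.* Bias needs unequal nonbleeding and one of the two routes in the working. The documents establish neither.
- *Nonbleeding is expected to differ by device.* The protocol counts and tests it. That allows for a difference but does not predict one.
- *The endpoint contradicts the full analysis set.* The article names the set without defining it, and the definition may stand in a fuller document. Excluding participants after three nonbleedings sits badly with that principle, but this is a tension and not a proven contradiction.
- *The bias is a known fraction of the planned effect.* That would need nonbleeding rates, an SD and a settled effect size, and the first two cannot be had from the article's text.

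**Conclusion.** The concern holds as a risk. The protocol fixes a scoring rule that leaves nonbleeding punctures unscored, mixes first and repeat punctures in the primary comparison, and leaves a device without a score after three failures. Neither the paired test nor LOCF repairs this.

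The device comparison can be biased in either direction, and the size is unknown. Across the assumed scenarios it ran from −3.1 to +6.1 mm, with the outer values resting on large differences in nonbleeding or on both routes acting together. It is nil with equal rates and the same repeat-puncture behaviour for both devices, and small if failures are rare. The rule is worth changing because the change is cheap and unrecorded scores cannot be recovered. The documents do not show that the trial's result would be invalid without it.

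**What to change.** 1. Record VAS, VRS and time to pain disappearance after every puncture, whether or not it bleeds, together with the attempt number.
2. Pre-specify an analysis of first-puncture VAS on each hand in all randomised participants, reported beside VAS at the successful puncture.
3. Keep participants with three nonbleedings in the first-puncture analysis. If a second hand is never punctured, state how the incomplete pair is handled.
4. Do not use LOCF to carry a score from one device to the other.
5. Leave it to the sponsor whether first-puncture VAS becomes the primary endpoint, given the weakness noted under the objection.

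The change adds no puncture or visit and leaves the repeat and stopping rules untouched. It costs a few extra entries on the case report form and an amendment. Study design (2.1) says that recruitment began in October 2019, so the amendment would come after enrolment had started. Scores for failed punctures already performed cannot be recovered. The report should therefore state from which participant the new recording applies.
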